## Abstract

**Background:**

Cool dialysate is often recommended for prevention of intra-dialytic hypotensive episodes in maintenance hemodialysis (HD) patients. However, its effect on toxin removal is not studied. It is known that inter-compartmental resistance is the main barrier for toxin removal. Cool dialysate can potentially increase this resistance by vasoconstriction and thus impair the toxin removal. The aim of this trial is to compare the toxin removal outcome associated with cool vs. warm dialysate.

**Method/design:**

This study is based on the hypothesis that dialysate temperature, a potential maneuver to maintain hemodynamic stability during HD, may influence inter-compartmental resistance and hence, toxin removal. Only stable HD patients will be recruited for this study. The quantum of removed toxins will be assessed by the total spent dialysate, which is a gold standard to quantify the efficacy of a single dialysis session. Collected samples will be analyzed for urea, creatinine, phosphate, β_2_-microglobulin, and uric acid. The study is a single center, self-controlled, randomized prospective clinical research where 20 study subjects will undergo 2 dialysis sessions: (a) cool dialysis with dialysate at 35.5°C, and (b) warm dialysis with dialysate at 37°C. Pre- and post-dialysis blood samples will be collected to quantify the dialysis adequacy and toxin reduction ratio.

**Discussion:**

This is the first clinical research to investigate the effect of dialysate temperature on removal of both small and large-sized toxins. Successful completion of this research will provide important knowledge pertaining to dialysate temperature prescription. Results can also lead to the hypothesis that cool dialysate may help in by preventing intra-dialytic hypotensive episodes, but prolonged prescription of cool dialysate may lead to comorbidities associated with excess toxin accumulation. The new knowledge will encourage for personalized dialysate temperature profiling.

**Trial registration:**

Clinicaltrials.gov Identifier - NCT02064153.

## Background

Improving toxin removal can potentially improve the hemodialysis (HD) patient outcome. In this context, the decades old HD procedure progressed from low efficiency low-flux dialysis to high efficiency high-flux dialysis and currently towards increased acceptance for convection based hemodiafiltration (HDF). However, in all these extracorporeal renal replacement therapies, toxin removal is primarily impaired by inter-compartmental resistance [1,2]. Overcoming this resistance seems to be the single most effective method for improved toxin removal. Intra-dialytic exercise may reduce this resistance by vasodilation. Exercise increases the cardiac output and reduces peripheral vascular resistance as the vasculature dilates. This vasodilation may be augmented by increased body core temperature due to exercise [3]. However, intra-dialytic exercise is still considered an intervention in routine dialysis setting, not a norm. Also, HD patients with significant muscle wasting may not be able to exercise during dialysis. How then can we induce the vasodilation without exercise or can we increase the body core temperature without exercise?

Dialysate temperature is an easy maneuver which can change the blood temperature, a surrogate of body core temperature. Warm dialysate can increase the body core temperature, resulting in vasodilation and increased mobilization of sequestered toxins to intravascular compartment. The contrary physiological change i.e. vasoconstriction can similarly be induced by cool dialysate and this is often recommended for prevention of intra-dialytic hypotensive (IDH) episodes. IDH is defined as a fall in systolic blood pressure below 90 mmHg or a drop of more than 20 mmHg that results in clinical symptoms, and occurs in 20-30% of treatments [4-6]. Cool dialysate induced vasoconstriction may reduce the toxin mobilization from remote inaccessible body compartments to intravascular compartment, thus hindering the toxin removal, which is contrary to the fundamental objective of HD. Hence, although cool dialysate helps in prevention of intra-dialytic episodes in short-term, prolonged usage may lead to poor patient outcome by impaired toxin removal. If cool dialysate does hinder toxin removal, then for at least 70-80% non-hypotensive HD patients, the benefits of warm dialysate may be realized.

Few studies have investigated the effect of cool dialysate on urea removal, and found that urea based dialysis adequacy is largely unaffected by dialysate temperature [7,8]. Nevertheless, it is suggested that urea based adequacy marker is not a true representative of toxins removal [9,10], as urea is too small in size and experiences negligible inter-compartmental resistance. Urea kinetics can also be explained by perfusion term or by regional blood flow alone [11,12], i.e. change in inter-compartmental resistance will have little effect on its mobilization. The same does not apply for large-sized toxins [13]. Even other small-sized toxins do not conform to the kinetic behavior shown by urea [14,15]. Interestingly, a clinical trial pertaining to removal of both small and large sized toxins via dialysate temperature manipulation has never been performed until now. Hence, the aim of this clinical study is to compare the toxin removal outcome for cool vs. warm dialysate for both small and large-sized toxins.

## Methods and design

### Study design and settings

The study is a single center, self-controlled, randomized study involving patients undergoing conventional high-flux dialysis. Patients are not informed about the dialysate temperature *a priori*; however, some subjects may report the warm or cool sensation based on their experience. The study will be conducted at satellite dialysis center of the National University Hospital (NUH), Singapore.

### Ethics approval and quality assurance

The domain specific review board affiliated with the National Healthcare Group (NHG), Singapore has approved the trial. The study will undergo routine quality assurance review conducted by the ethics board. The ethics board will also receive timely progress status report from the principal investigator and will be promptly informed of any adverse events owing to the study intervention. The grantor will also receive timely report of study progress.

### Patient recruitment

The warm dialysate may result in IDH episodes; hence, only stable HD subjects with no prior history of IDH will be recruited for the proposed study. The dialysis nurses will provide the list of all stable patients in the past one month. The principal investigator will review the database of these stable patients. The patients with history of angina, heart-attack, or chronic obstructive pulmonary diseases (COPD) will not be recruited for the trial. Though stable on HD, these patients may be unstable during warm dialysis session. The residual renal function of study subjects should be negligible (defined by urine output of less than 200 mL/day). Only those subjects, who follow 3 times per week dialysis schedule, will be recruited. Subjects satisfying our mentioned criteria will be contacted. The study administrator will explain about the intervention and the potential benefits as well as harms. Agreed subjects will sign the patient information sheet and consent form. A copy of the consent form will be provided to the subject. Total 20 subjects will be recruited for the study.

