### Exclusion criteria

History of recurring or persistent hypotension in the past 1 monthPregnant womanSeverely hypertensive patients (SBP > 180 mmHg and/or DBP > 115 mmHg)Severely hypotensive patients (SBP < 100 mm Hg and/or DBP < 60 mmHg)Paradoxically hypertensive patients whose BP increases by more than 20% of baseline during dialysis (in the past 1 month)History of recent myocardial infarction or unstable angina (within the past 6 months)Significant valvular disease, i.e. severe aortic stenosis and moderate-severe mitral regurgitationPatients with end stage organ disease e.g. COPD, recent or debilitating CVAPatients with Left Ventricular dysfunction, Chronic Heart Failure and older age group more than 70 yearsPatient with recent stroke (within the past 6 months)History of known arrhythmiaParticipation in another clinical intervention trialUnable to consent

Dialysis hypotension may occur in one of three clinical patterns: (i) acute (episodic) hypotension defined as a sudden drop of systolic blood pressure below 90 mmHg or of at least 20 mmHg with accompanying clinical symptoms, (ii) recurrent – as detailed above but prevailing in a minimum 50% of dialysis sessions, and (iii) chronic, persistent hypotension in which interdialytic systolic blood pressure is maintained at less than 90–100 mmHg.

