### Treatment modification

Study sessions will be discontinued, should adverse-effects such as acute hypotensive episode (defined by sudden change in blood pressure – drop of 20 mm Hg or SBP < 100) or chest pain, uneasiness, or cramps manifest. Although these are anticipated to be at low event occurrence rate, the event will be medically recorded and dealt with usual clinical practice. During the session, if a patient complains about temperature being too high or too low, then the dialysate temperature will be adjusted to his/her routine prescription and subject will be removed from the study. A report of all such adverse events will be provided to the ethics board.

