It has been mentioned that blood cooling has adverse effect on solute disequilibrium [12]. In a study of unstable HD patients, cool dialysate (35°C) was associated with significantly greater increase in peripheral vascular resistance [17]. This increased vasoconstriction can potentially reduce the mobilization of toxins from remote compartments to intravascular compartment, thus reducing the dialysis efficacy. Cool dialysate may be good for 4 hour dialysis, but, in the long term, it may culminate into various complications due to less efficient removal of uremic toxins. One such co-morbidity is amyloidosis due to prolonged accumulation of middle molecule marker, β_2_-microglobulin. It will not be wrong to say that cool dialysate focuses only on one aspect of the dialysis treatment i.e. prevention of IDH, but it must be weighed against the plausible unwanted negative influence of impairing an equally important aspect of treatment i.e. uremic toxin removal. Effect of cool dialysate on urea clearance has been studied, and its removal was not significantly affected by cool dialysate [4,7,18,19]. It is because urea is too small in size to experience significant inter-compartmental resistance from cellular membrane and/or capillary endothelium. Also, the rapid equilibration of urea across the cell membrane is essentially due to facilitated transport by selective urea transporters [20]; such transporters do not exist for other similar sized toxins. Hence, it is imperative to study the effect of dialysate temperature on toxin removal other than urea. Interestingly, there is no clinical study which has investigated the effect of dialysate temperature on toxin removal. The proposed clinical trial intends to fill the gap by comparing the toxin removal outcome for cool and warm dialysate. Contrary to cool dialysate induced vasoconstriction, warm dialysate will result in vasodilation and open capillary surface. This will contribute towards enhanced toxin mobilization from remote inaccessible compartments to intravascular compartment and their subsequent removal in the dialyzer. One should also note that warm dialysate may result in incidence of IDH, and so only stable on HD subjects will be recruited for the trial.

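### The safety criterion for the 37°C session is stated in two conflicting ways: no prior IDH at all, or only no recurring or persistent hypotension in the last month

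*Protocol article*

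**What the plan says.** The Patient recruitment section gives both the risk and the rule: "warm dialysate may result in IDH episodes; hence, only stable HD subjects with no prior history of IDH will be recruited". It then describes the screening. The dialysis nurses list the patients who were stable over the past month, and the principal investigator reviews the database of those patients.

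The Inclusion criteria require stability on haemodialysis without defining it. The Exclusion criteria bar a history of hypotension that was recurring or persistent, limited to the past month. A separate item bars patients with SBP < 100 and/or DBP < 60 mmHg.

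The text under the exclusion list defines three patterns of dialysis hypotension:
- **Acute:** "acute (episodic) hypotension defined as a sudden drop of systolic blood pressure below 90 mmHg", or a drop of at least 20 mmHg with symptoms.
- **Recurrent:** "as detailed above but prevailing in a minimum 50% of dialysis sessions".
- **Chronic, persistent:** interdialytic systolic pressure held below 90–100 mmHg.

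The Discussion repeats the reason with a weaker condition: "warm dialysate may result in incidence of IDH, and so only stable on HD subjects will be recruited for the trial".

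**The concern.** The criterion exists to keep patients prone to IDH out of a session that may provoke it. The two statements of it differ on two counts:
- **Time window:** ever, against the past month.
- **Severity:** any episode, against recurrence in at least half of sessions or a persistently low pressure.

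The document does not say which statement governs. Screening staff normally work from the numbered or bulleted lists, and here the list is the looser version. The nurses' list has the same one-month horizon, so nothing in the described workflow clearly prompts anyone to look further back. What is at stake is mainly subject safety: a patient whom the recruitment text regards as unsuitable could be given 37°C dialysate because the list let that patient through.

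**Working it through.** No sample size, power or alpha is in dispute, and the protocol gives no figure to reproduce. The check is a comparison of texts, with one small count.

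**Step 1: what counts as IDH.** The Background section defines IDH as systolic pressure falling below 90 mmHg, or a symptomatic drop of more than 20 mmHg. The acute pattern under the exclusion list is essentially the same event (it says at least 20 mmHg). A single acute episode is therefore a prior history of IDH under the recruitment rule.

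**Step 2: the rules side by side.**

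| Patient's history | Patient recruitment rule | Exclusion line on hypotension history |
|---|---|---|
| No IDH ever | eligible | eligible |
| Acute episodes in the past month, in fewer than 50% of sessions | not eligible | eligible |
| Any IDH, but only more than a month ago | not eligible | eligible |
| Recurrent IDH (at least 50% of sessions) in the past month | not eligible | not eligible |

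The rules disagree in the second and third rows.

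**Step 3: how wide the second row is.** The Patient recruitment section requires a three-times-weekly schedule: "Only those subjects, who follow 3 times per week dialysis schedule, will be recruited". Taking a month as 4 weeks gives 4 × 3 = 12 sessions. Taking it as 52/12 = 4.33 weeks gives 4.33 × 3 = 13 sessions.
- 12 sessions: 50% is 6, so recurrence needs 6 episodes, and 1 to 5 pass the list line.
- 13 sessions: 50% is 6.5, so recurrence needs 7 episodes, and 1 to 6 pass the list line.

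All of these patients fail the recruitment rule. The count describes how far apart the rules are, not how many patients fall between them.

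**Step 4: whether other criteria close the gap.**
- The SBP/DBP exclusion concerns a pressure level. A patient with acceptable pressures can have had earlier acute episodes.
- Stability on haemodialysis might screen out some patients with recent episodes. It is not defined, and the nurses' list applies it to one month only.
- The investigator's database review could catch older IDH, but the text does not say that it looks back beyond the month.

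**Step 5: whether the mismatch is isolated.** The same split appears for cardiac history. The recruitment text bars any history of angina or heart attack, while the list bars recent myocardial infarction or unstable angina within 6 months. The list is again the looser statement.

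**The case against.** The strongest reply is that the rules are cumulative. A patient with no prior IDH also passes the exclusion line, so both can be met at once and the stricter one decides. The Patient recruitment section plainly works as eligibility text: the urine-output limit and the thrice-weekly schedule are set there and appear in neither list. A reader who used the lists alone would miss those rules too. This stands, and on that reading most of the gap closes. What remains is that the exclusion line becomes largely redundant, the document never says which statement prevails, and the one-month screening list supports the looser one.

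It is also fair that the Discussion sentence is a summary and not a third criterion. Further protections exist: no Monday or Tuesday sessions, stopping rules, and blood pressure and heart rate recorded every 5 minutes. The last two act only once the session is running.

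Two stronger readings are tempting, and the documents do not support them.
- **A reader might infer that the plan is wrong not to ask at what dialysate temperature a patient was stable.** The abstract says that "Cool dialysate is often recommended for prevention of intra-dialytic hypotensive episodes in maintenance hemodialysis (HD) patients", and the Treatment modification section provides that after a temperature complaint "the dialysate temperature will be adjusted to his/her routine prescription and subject will be removed from the study". The recruitment text also accepts, for patients with angina, heart attack or COPD, that "Though stable on HD, these patients may be unstable during warm dialysis session". But patients cooled because of earlier IDH already fail the recruitment rule. Nothing shows that this centre has patients cooled purely as prevention, with no IDH on record. A routine prescription need not be a cooled one, and the Discussion's remark about a one-size-fits-all approach suggests that temperatures may be uniform. This is an optional precaution, not an error.
- **A reader might try to put a number on the harm**, for instance by applying the Background's 20–30% IDH rate per treatment to the candidates. That rate is general, IDH clusters within patients, and the pool is pre-selected as stable. The documents support no estimate of how many unsuitable patients would be enrolled or how many pairs would be lost.

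**Conclusion.** The inconsistency is real and concerns the criterion that controls the intervention's own named risk. The recruitment rule bars any prior IDH. The listed exclusion leaves out acute episodes, and it leaves out anything older than a month. The other criteria do not restore the stricter rule.

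The size is modest. If staff apply the whole recruitment section, the stricter rule governs and no unsuitable patient should enter. If they screen from the lists and the one-month nurses' list, patients with occasional or older IDH could be enrolled. The number is unknown and may be small. The point rests on the text alone, apart from taking a month as 12 or 13 sessions. It should be corrected because the criterion matters and the correction is cheap, not because harm has been shown.

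**What to change.** Reword the exclusion line to match the recruitment rule, for example: any previous intra-dialytic hypotension, including acute episodes as defined below, without a time limit. State that the principal investigator's database review checks IDH history beyond the past month.

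This adds no restriction that the protocol does not already state. It costs one reworded line and a longer look at records already held. If the one-month screen was what the sponsor intended in practice, enforcing the written rule shrinks the eligible pool at a single centre that needs 20 subjects. In that case the sponsor should instead relax the recruitment text openly and justify why a one-month screen is safe enough for 37°C, rather than leave both versions standing.

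As an optional precaution, also check the dialysis record and exclude patients whose dialysate temperature was lowered to treat or prevent hypotension, since stability on cooled dialysate does not show tolerance of 37°C. This would be a new restriction. The number affected may be zero, and the results would say less about patients who are routinely cooled.

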### Inclusion criteria

Adult patients male or female (Age > 21 years, Age < 70 years)Minimum dialysis vintage of 3 monthsStable on hemodialysisBlood access capable of delivering the blood flow rate greater than 250 mL/min

### Exclusion criteria

History of recurring or persistent hypotension in the past 1 monthPregnant womanSeverely hypertensive patients (SBP > 180 mmHg and/or DBP > 115 mmHg)Severely hypotensive patients (SBP < 100 mm Hg and/or DBP < 60 mmHg)Paradoxically hypertensive patients whose BP increases by more than 20% of baseline during dialysis (in the past 1 month)History of recent myocardial infarction or unstable angina (within the past 6 months)Significant valvular disease, i.e. severe aortic stenosis and moderate-severe mitral regurgitationPatients with end stage organ disease e.g. COPD, recent or debilitating CVAPatients with Left Ventricular dysfunction, Chronic Heart Failure and older age group more than 70 yearsPatient with recent stroke (within the past 6 months)History of known arrhythmiaParticipation in another clinical intervention trialUnable to consent

Dialysis hypotension may occur in one of three clinical patterns: (i) acute (episodic) hypotension defined as a sudden drop of systolic blood pressure below 90 mmHg or of at least 20 mmHg with accompanying clinical symptoms, (ii) recurrent – as detailed above but prevailing in a minimum 50% of dialysis sessions, and (iii) chronic, persistent hypotension in which interdialytic systolic blood pressure is maintained at less than 90–100 mmHg.

### Study interventions and randomization

All recruited subjects will undergo two study sessions: (i) cool dialysis with dialysate temperature at 35.5°C and (ii) warm dialysis with dialysate temperature at 37°C. The dialysis duration for all sessions will be 240 min. In total, 40 study sessions will be conducted. The maximum and minimum interval between two sessions respectively is one month and one week. Minimum of one week gap is maintained to avoid any carry over effect from the previous study session. All dialysis sessions will be performed using high flux (single-use) dialyzer and the Fresenius 4008S machine. Except dialysate temperature, the dialysis prescription and patient medications (phosphate binder, medicine for hypertension, erythropoietin, etc.) will remain unchanged. Patients will also be advised to keep their dietary intake fairly constant during the study period.

Patients are generally fluid overloaded on the beginning of the week i.e. Monday/Tuesday and target ultrafiltration (UF) will generally be set higher on those days. This higher fluid removal requirement may sometimes result in cramps or hypotensive episodes. Warm dialysate may aggravate this situation by vasodilation; hence, no study session will be performed on Monday/Tuesday. The study sessions for a particular patient will be performed on the same day of the week. All the study sessions will be conducted in randomized order, but patient’s existing dialysis schedule will not be disturbed for the purpose of the study.

### Data collection

#### Blood and dialysate sampling

During each study session, pre- and post-dialysis blood samples will be collected. These samples will be analyzed for both small and large-sized uremic toxins, namely, urea, creatinine, phosphate, β_2_-microglobulin, and uric acid. The dialysate flow will be kept at 500 mL/min. Total spent dialysate will be collected in a large container. To assess the quantum of removed toxin mass in a particular study session, the spent dialysate will be analyzed for the mentioned toxins. The spent dialysate collection is the gold standard to ascertain session adequacy. All the samples will be sent to NUH Laboratory Medicine Department for analysis. The pre- and post-dialysis blood samples will be used for calculating the toxin reduction ratio and urea based dialysis adequacy.

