### Outcome measure

#### Primary outcome measure

The objective of this clinical study is to investigate the effect of dialysate temperature on removal of both small and large-sized toxins. To quantify the removed toxin mass in an individual study session, the spent dialysate sample will be analyzed for toxin concentration. The removed toxin mass will potentially depend on the pre-dialysis toxin concentration. If pre-dialysis toxin concentration is high then there is a possibility that more toxin mass will be removed; hence removed toxin mass assessed by spent dialysate will be scaled with respect to pre-dialysis serum toxin concentration. This scaled removed toxin mass for both study sessions will be compared using standard statistical *t*-test. The toxin reduction ratio will also be calculated using pre- and post-dialysis toxin concentrations.

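### The beta-2-microglobulin reduction ratio, as stated, takes no account of fluid removed: it reads low and gains some session-to-session noise, but the t-tested outcome is unaffected

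*Protocol article*

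**What the plan says.** All references are to the protocol article.

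- **How the ratio is formed.** Blood and dialysate sampling states: "The pre- and post-dialysis blood samples will be used for calculating the toxin reduction ratio and urea based dialysis adequacy". Primary outcome measure repeats it: "The toxin reduction ratio will also be calculated using pre- and post-dialysis toxin concentrations". Neither place mentions weight, ultrafiltration or haemoconcentration.
- **Which solutes.** "These samples will be analyzed for both small and large-sized uremic toxins"; the five listed include beta-2-microglobulin, the large-solute marker.
- **What is tested.** Under Primary outcome measure, the mass found in the total spent dialysate is scaled to the pre-dialysis serum concentration, and "This scaled removed toxin mass for both study sessions will be compared using standard statistical *t*-test". The reduction ratio follows as an additional measure.
- **What limits differences in fluid removal.** Study interventions and randomization notes that patients carry more fluid at the start of the week and that "target ultrafiltration (UF) will generally be set higher on those days". It then rules those days out ("no study session will be performed on Monday/Tuesday") and fixes the weekday within a patient: "The study sessions for a particular patient will be performed on the same day of the week". "Except dialysate temperature, the dialysis prescription and patient medications" are to stay as they were, and session order is randomized.

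The article gives no ultrafiltration volume, body weight, expected reduction ratio or expected temperature effect. It does not say that the volume removed will be equal in a patient's two sessions.

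**The concern.** Ultrafiltration shrinks the extracellular space. A solute held mainly in that space becomes more concentrated as the space shrinks, even while it is being cleared. The post-dialysis concentration is then higher than clearance alone would leave it, and a ratio built on concentrations is too low.

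This matters most for beta-2-microglobulin. The Background argues that urea is a poor marker and that larger solutes face more inter-compartmental resistance. The Discussion names beta-2-microglobulin accumulation as the long-term worry with cool dialysate. Readers are therefore likely to look at this ratio closely.

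Two things are at stake: the absolute level of the reported ratio, and the comparison between temperatures if fluid removal differs between a patient's sessions.

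**Working it through.** There is no figure in the article to reproduce, so the size of the effect is computed from assumed inputs.

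**Inputs**
- From the article: 20 patients with two sessions each; ratio formed from pre- and post-dialysis concentrations.
- Assumed: extracellular volume is 0.2 × post-dialysis weight; weight 60 kg (range 50–70); fluid removed (UF) 1–3 L; true (corrected) ratio 70% (range 60–80%).

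**1. Understatement in one session**

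Corrected post-dialysis concentration = measured value / (1 + UF/(0.2 × weight)). Rearranged:

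raw ratio = 1 − (1 − true ratio) × (1 + UF/(0.2 × weight))

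At 60 kg the extracellular volume is 0.2 × 60 = 12 L. With a true ratio of 70%:

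| UF | Calculation | Raw ratio | Shortfall (points) |
|---|---|---|---|
| 1 L | 1 − 0.30 × (1 + 1/12) | 67.5% | 2.5 |
| 2 L | 1 − 0.30 × (1 + 2/12) | 65.0% | 5.0 |
| 3 L | 1 − 0.30 × (1 + 3/12) | 62.5% | 7.5 |

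Over the whole assumed range the shortfall runs from 0.20 × 1/14 = 1.4 points (70 kg, 1 L, true ratio 80%) to 0.40 × 3/10 = 12 points (50 kg, 3 L, true ratio 60%).

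**2. Sensitivity to a difference in UF between one patient's sessions**

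Shift = (1 − true ratio) × difference in UF/(0.2 × weight).

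For 0.5 L at 60 kg and 70%: 0.30 × 0.5/12 = 1.25 points. Over the range: 0.7–2.0 points for 0.5 L, and 1.4–4.0 points for 1 L.

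**3. Effect on the mean of 20 paired differences**

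Suppose UF differences are unrelated to temperature.
- SD 0.5 L: SD of the ratio difference 1.25 points; standard error 1.25/√20 = 0.28; 95% half-width 2.093 × 0.28 = about 0.6 points.
- SD 1.0 L: SD 2.5 points; standard error 2.5/√20 = 0.56; half-width about 1.2 points.

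**4. What pairing removes**

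If UF is the same in both sessions, the raw difference is the true difference × (1 + UF/(0.2 × weight)). At 2 L and 60 kg the factor is 1 + 2/12 = 1.17. The 5-point shortfall drops out, and the difference is only rescaled.

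**5. A yardstick for the temperature effect**

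The article gives none. Purely as an illustration, take ratio = 1 − exp(−Kt/V). At 70%, a 5% relative gain in Kt/V gives 1 − 0.30^1.05 − 0.70 = about 1.75 points, and a 10% gain gives about 3.4 points.

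**The case against.** **The article is condensed and does not say the concentrations are uncorrected.** A corrected ratio is also built from pre- and post-dialysis concentrations, and the full protocol might carry the correction. This stands as a caution. The article does, however, state the inputs in two places and names only concentrations, so anyone following it as written would compute the uncorrected ratio.

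**The design already limits the problem.** Fixed weekday, no start-of-week sessions, an unchanged prescription and randomized order should make differences in fluid removal within a patient mostly modest and unrelated to temperature. The article's remark on higher ultrafiltration concerns the very days it excludes. This stands, although equal volume is not promised and the two sessions may be up to one month apart.

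**The tested outcome is untouched.** This stands in full: scaled dialysate mass does not use the post-dialysis sample.

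**Two stronger readings are tempting, and the article supports neither.**
- A reader might infer that the distortion is as large as the temperature effect. The article gives no expected effect, volume or weight to compare. The 1.25-point figure is a shift in a single patient. For the mean of 20 pairs, the matching noise is a standard error of about 0.28 points, well below the illustrative 1.75 points for a 5% gain in Kt/V.
- A reader might infer a bias towards warm dialysate because less fluid would be removed when blood pressure falls. The actions stated under Treatment modification and Secondary outcome measure are to discontinue or suspend the session, not to reduce ultrafiltration. Stopping early pushes the ratio the other way. Assume first-order removal, a stop at 180 of 240 minutes and UF cut in proportion from 2.5 to 1.875 L at 60 kg. The true ratio falls from 70% to 1 − 0.30^0.75 = 59%, and the raw ratio falls from 64% to 1 − 0.405 × (1 + 1.875/12) = 53%, despite less fluid removed. Lower UF over a full-length session would raise the ratio, but nothing in the article predicts it.

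**Conclusion.** The point holds as a minor one about an additional measure. Calculated as the article states, the beta-2-microglobulin reduction ratio is too low whenever fluid is removed, by roughly 2.5 to 7.5 points in the central case, and its value depends on each session's ultrafiltration.

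For the comparison of temperatures, the expected consequence is extra noise rather than bias, unless temperature itself changes the fluid removed. The main result of the trial does not depend on it.

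The direction follows from the physiology and the stated inputs. Every size rests on the assumed weight, volume, true ratio and 20% extracellular fraction, none of which the article supplies.

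**What to change.** For beta-2-microglobulin only, state that the post-dialysis concentration will be divided by 1 + weight loss/(0.2 × post-dialysis weight) before the reduction ratio is computed, with both weights in kg. Report the raw and the corrected ratio side by side. Tabulate ultrafiltration volume by dialysate temperature, so that readers can see whether fluid removal differed between the two conditions.

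The cost is one formula plus pre- and post-session weights, with no new blood or dialysate samples. The article does not list weights among the recorded data, so their collection should be confirmed. The drawback is that the correction relies on an assumed extracellular fraction, which is a reason to keep the raw ratio in the report.
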